### Qualitative analysis

Qualitative data from the Satisfaction questionnaire will be transcribed and anonymised to maintain confidentiality. Data will then be analysed iteratively using focussed thematic analysis [66]. Three members of the research team will independently code initial data before constructing an analytic framework around: i) facilitators/barriers to engagement, previous experiences of psychotherapy, and adaptations to ACT for plwMND; and ii) the acceptability, relevance, perceived value and feasibility of delivering ACT to plwMND. The analytical framework will be applied to the remaining transcripts, with themes and subthemes refined as necessary.

### Economic evaluation

A cost-utility analysis will present the incremental costs per quality-adjusted life years from an NHS and social care perspective of plwMND receiving ACT plus UC compared to those receiving UC alone. Costs will be estimated for each participant with MND and will include costs for delivering the intervention (training and staff time for delivering the intervention, cost of materials) and primary and secondary health care usage. Data on health care resource use will be collected using the modified CSRI and will collect information on hospital, nursing home and hospice services, out-patient visits and day care, primary and community care services, and equipment obtained. Unit costs will be derived from appropriate national sources and will include NHS reference costs and Personal Social Service Research Unit costs [67, 68]. The standard version of the EQ-5D-5L will be used to collect utility values, which will be used to estimate quality-adjusted life years. These will be calculated using the area under the curve method. Where data on the EQ-5D-5L or resource use are missing, multiple imputation techniques will be implemented. Differences between costs and quality-adjusted life years in the two groups will be described and the incremental cost effectiveness ratio will be calculated. A trial-based analysis will be supplemented by an analysis using a simple decision analytic model (a Markov model), which will be used to estimate the cost effectiveness of the intervention over the lifetime of plwMND. The model will use transition states related to the severity of MND (mild, moderate, severe, terminal and death) and will use a two-month cycle. It will be based on previous models published in the literature. This will be populated using the trial data plus information from the literature where required. This analysis will allow the estimation of lifetime cost-effectiveness and associated cost-effectiveness acceptability curves through the use of probabilistic sensitivity analysis. Caregiver costs will be included in a secondary analysis which will take a wider perspective to include patient and caregiver burden. Sensitivity analysis will explore assumptions made around transition probabilities, costs and long-term survival estimates. Bootstrapping will be used to capture uncertainty around cost-effectiveness estimates.

### Patient and Public Involvement (PPI)

PPI members are and have been involved at all stages of the study. The intervention was initially developed through a combination of interviews and workshops comprising people with MND, caregivers of people with MND and MND healthcare professionals. Five interested plwMND and caregivers were invited to be members of the study’s Patient/Caregiver Advisory Group. The intervention has been developed and refined in close collaboration with them, and they have also advised on research management, trial documents and dissemination of findings. PPI members attend Patient/Caregiver Advisory Group and Trial Management Group meetings, while independent plwMND and representatives from the MND Association attend TSC meetings.

### Data monitoring

The study will be conducted in line with the Helsinki Declaration. University College London is the nominated sponsor and research governance will be led by the UCL/UCLH Joint Research Office ([contact]). The study will be conducted in accordance with the protocol, Good Clinical Practice and Sheffield CTRU SOPs. All trial related documentation will be made available on request to the sponsor, Health Research Authority, Research Ethics Committee and other relevant authorities. An independent TSC (comprising academic clinicians, a statistician, a health economist and PPI representatives) and an independent DMEC (comprising academic clinicians and a statistician) will meet every 6–12 months to review progress and monitor the trial. All safety data will be reviewed by the DMEC. There will be no planned interim analyses.

### Safety

Trial sites will report Adverse Events (AEs) and Serious Adverse Events (SAEs) in accordance with Sheffield CTRU SOPs. These will be reported at any stage of trial participation, as well as at 6- and 9-months follow-up. An AE will be defined as any untoward medical occurrence in a trial participant with MND. All incidents of non-physical AEs will be collected and recorded, while physical AEs other than physical self-harm will not be as they are expected in this population. All SAEs will be reported to Sheffield CTRU and the sponsor within 24 h of discovery at site: those deemed both “unexpected” and “related” to the intervention or trial will be reported to the REC within 15 days of being reported to the study team.

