## Acceptance and commitment therapy

A detailed breakdown of the ACT intervention is provided in Supplementary File 3. PlwMND will receive up to eight 1:1 sessions of ACT, each lasting up to 1 h, over the course of four months. A minimum of four sessions will be face-to-face (delivered within the MND clinic, GP surgery or participant's home, or via videoconference, depending on patient preference and therapist availability) and up to four will be delivered via online audio material/CDs (followed by therapist support via videoconference, instant messaging, telephone or email, depending on patient preference). In exceptional circumstances, all sessions may be delivered via telephone where videoconference facilities are not available (e.g. due to COVID-19). A phased ending to the sessions will be incorporated such that they will be weekly for the first six sessions and then fortnightly for the last two sessions. Should participants not complete their sessions within four months, they will still be offered the opportunity to complete up to eight sessions and the number of weeks taken to deliver the intervention will be recorded.

The intervention will be delivered by Band 7 or Band 8 clinical psychologists, counselling psychologists, counsellors or psychotherapists with training in Cognitive Behavioural Therapy or accredited Cognitive Behavioural Therapy therapists, with a minimum of 1 year experience in delivering psychotherapy interventions. Therapists will attend a 4-day experientially-based training workshop on the use of ACT in plwMND, supplemented by freely available online ACT resources and copies of the newly-developed participant workbook, therapist manual and online videos. Training will be delivered by members of the research team with expertise and experience in ACT and MND, and will also include two interested members of the Patient/Caregiver Advisory Group, where possible. After completing training and achieving satisfactory competence in ACT delivery, therapists will deliver ACT for plwMND under fortnightly group supervision via telephone/video call from a Band 8 equivalent clinical psychologist or psychotherapist trained in ACT, with a minimum of five years’ experience in delivering this therapy. Therapists will also attend a 1-day top-up training course after 12 months to review and consolidate skills in delivering ACT to plwMND.

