## Usual multidisciplinary care

UC will comprise standard care as outlined in NICE Clinical Guideline NG42 for MND [13], as this is currently what is available within UK healthcare services for plwMND. This will include medication for managing MND and MND-related symptoms, treatments for MND-related symptoms (e.g. physiotherapy, non-invasive ventilation and gastrostomy), and equipment and adaptations to aid activities of daily living, communication and mobility. Coordinated care will be delivered by multidisciplinary healthcare professionals within MND and palliative care services and will include access to other services (including clinical psychology and neuropsychology, counselling, social care, respiratory ventilation, palliative care gastroenterology, orthotics, mobility/assistive technology/communication equipment services and community neurological care teams). All of the MND Care Centres/clinics involved as recruiting sites are endorsed by the MND Association, and therefore are audited against the standard of care outlined in NICE Clinical Guideline NG42 [13].

As some variations in UC may occur, this will be monitored using a modified form of the Client Service Receipt Inventory (CSRI) [42]. Participants in the intervention arm will be asked to refrain from engaging in concurrent formal psychological therapies such as CBT during the receipt of ACT as this may lead to conflicts in therapeutic approaches and goals. Other than this, participants will not be actively discouraged from seeking treatment outside of the trial for ethical reasons, but all such interventions will be recorded as part of the modified CSRI.

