Secondary outcome measures will be as follows:Hospital Anxiety and Depression Scale [50]: A 14-item self-report measure of depression and anxiety, which provides separate scores for depression and anxiety, as well as an overall score. For the purpose of analysis and, following validation in plwMND and subsequent published recommendations [51], a subset of data will be analysed which omits one item on the depression scale that assesses psychomotor retardation and one item on the anxiety scale that assesses restlessness as these overlap with physical symptoms of MND;Acceptance and Action Questionnaire-II [52]: A 7-item self-report measure of psychological flexibility (an ACT-specific coping measure);EQ-5D-5L [53]: A 5-item self-report measure of health-related quality of life, used to calculate utility scores for use in economic evaluations. Each of the 5 items is rated on a 5-point scale from no problems to extreme problems. This will be collected from both plwMND and caregivers;Non-physical adverse events and physical self-harm;ALS Functional Rating Scale-Revised [54]: The self-administered version of a 12-item measure of function that has been developed for plwMND will be used as an indicator of disease progression;Existential and Psychological subscales of the McGill Quality of Life Questionnaire-R [45]^,2^: These subscales have been included as secondary outcome measures as quality of life in MND (and hence psychological health) has been found to be more associated with psychological/existential factors than physical function/strength [49];Survival at 9 months;Satisfaction with Therapy and Therapist Scale-Revised [55]: A 12-item self-report measure of satisfaction with therapy and satisfaction with the therapist, rated on a 5-point scale from 1 (strongly disagree) to 5 (strongly agree). Six items relate to satisfaction with therapy and six to satisfaction with the therapist;Client Service Receipt Inventory (CSRI) [42] modified for plwMND. This information will be extracted from participants' self-reports, GP medical records and/or MND care centre records, with participants' consent;Quality-adjusted life years and resource use to inform the cost-effectiveness analysis;Zarit Burden Interview [56]: A well-validated 22-item self-report measure of caregiver burden, which will only be collected from caregivers.

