### Quantitative analysis

A statistical analysis plan that includes the health economic analysis will be developed a priori and reviewed and approved by the Trial Steering Committee (TSC). The primary outcome measure will be analysed using a multi-level mixed effects model in which treatment group and baseline score will be included as fixed effect covariates and therapist will be included as a random effect to account for potential clustering. Analyses will be conducted separately at 6 months (the primary analysis time point) and 9 months. The difference between groups in mean quality of life will be quantified by the model coefficient, along with its 95% confidence interval. Primary analyses will be by intention to treat, but additional sensitivity analyses will be used to assess whether outcomes vary across sites/therapists, and by disease severity at baseline, psychotropic medication use, number of weeks taken to complete the therapy sessions and participants’ engagement in the intervention (as determined by the number of sessions completed within 4 months, and if applicable, whether the sessions were ongoing beyond 6 months post-randomisation).

Secondary outcome measures (for patients and caregivers) will be analysed in a similar fashion to the primary outcome measure. Adverse events will be summarised as the number and percentage of patients experiencing each event and the number of events by treatment arm. Patient deaths are expected to be relatively uncommon at 9 months (< 10%) and will be summarised descriptively as an adverse event. It is expected that some participants will have missing outcome data either due to death, loss to follow up or withdrawal from trial. The number of missing values will be summarised by treatment group, time point and reason. Multiple imputation using Rubin's rules [64] will be implemented for the primary and other key endpoints if the level of missing data exceeds 5% for reasons other than participant death.

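### Open-ended adverse event reporting, with up to eight extra contacts in the ACT arm only, may inflate recorded non-physical events in that arm, and the by-arm summary does not separate the routes

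*Protocol article*

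**What the plan says.** All references are to the protocol article.

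- **Who reports (Safety):** "Trial sites will report Adverse Events (AEs) and Serious Adverse Events (SAEs) in accordance with Sheffield CTRU SOPs". Study therapists are not named as a route.
- **When (Safety):** "These will be reported at any stage of trial participation, as well as at 6- and 9-months follow-up".
- **What is collected (Safety):** "All incidents of non-physical AEs will be collected and recorded, while physical AEs other than physical self-harm will not be". The Outcomes section lists this among the secondary outcomes: "Non-physical adverse events and physical self-harm".
- **How it is analysed (Quantitative analysis):** "Adverse events will be summarised as the number and percentage of patients experiencing each event and the number of events by treatment arm". No test is stated, and no split by the way an event was found.
- **Contacts in the ACT arm only (Acceptance and commitment therapy):** "PlwMND will receive up to eight 1:1 sessions of ACT, each lasting up to 1 h, over the course of four months". Of these sessions, "up to four will be delivered via online audio material/CDs", followed by therapist support. Sessions not finished in four months may still be completed later.
- **Contacts in both arms:** the Data collection section schedules follow-up at 6 and 9 months. Usual care, which both arms receive, is described under Usual multidisciplinary care: "Coordinated care will be delivered by multidisciplinary healthcare professionals within MND and palliative care services".
- **Blinding:** participants, carers, therapists and clinicians know the allocation.

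**The concern.** A by-arm comparison of event counts is fair only if an event has the same chance of being recorded in either arm. Here reporting is open throughout participation, but regular one-to-one contact during the first months exists in one arm only. The secondary outcome is also confined to the events most likely to be raised with a therapist, since physical events other than self-harm are excluded.

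If some of what is disclosed in therapy reaches the site as a report, the ACT arm will record more events at the same true risk. The single by-arm summary gives a reader no means of telling extra events from extra detection. An apparent excess could be read as harm from ACT. Equally, a true reduction in distress events under ACT could be partly or wholly hidden.

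**Working it through.** **No plan figure to reproduce.** The article states no adverse event rate, detection rate or ratio. The only design figure used here is 188 participants allocated 1:1, which is 188 / 2 = 94 per arm.

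**Trial contacts at which an event could surface.** Usual care alone: 2 (6 and 9 months). ACT plus usual care: 2 + up to 8 = up to 10. Usual care contacts are common to both arms, so they are left out of this count.

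**Model, assuming equal true risk p in both arms.**
- s = share of events found by routes common to both arms
- q = share of otherwise missed events, occurring in the therapy period, that are found through therapy
- w = share of events occurring in the therapy period; 4/9 if events are spread evenly over nine months and therapy fills the first four

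Recorded risk in usual care = p × s. Recorded risk in ACT = p × [s + (1 − s) × q × w]. Apparent ratio = 1 + (1 − s) × q × w / s. The values of s and q are assumptions.

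**Reference case, s = 0.5.**
- q = 0.30: 0.5 + 0.5 × 0.30 × 4/9 = 0.567; ratio 0.567 / 0.5 = 1.13
- q = 0.60: 0.5 + 0.5 × 0.60 × 4/9 = 0.633; ratio 0.633 / 0.5 = 1.27
- q = 0: ratio 1.00

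**As counts, taking p = 0.20 for illustration.** Usual care: 94 × 0.20 × 0.5 = 9.4 participants. ACT: 94 × 0.20 × 0.567 = 10.7 to 94 × 0.20 × 0.633 = 11.9.

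**Sensitivity.**

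| s (w = 4/9) | q = 0.30 | q = 0.60 |
|---|---|---|
| 0.5 | 1.13 | 1.27 |
| 0.7 | 1.06 | 1.11 |
| 0.9 | 1.01 | 1.03 |
| 1.0 | 1.00 | 1.00 |

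At the extreme of s = 0.5 and q = 1, the ratio is 1 + 4/9 = 1.44. If sessions overran so that therapy covered six of the nine months (w = 6/9), the reference case would give 1 + 0.30 × 6/9 = 1.20 to 1 + 0.60 × 6/9 = 1.40.

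**What could be hidden.** In the reference case, a true ACT to usual care risk ratio of 0.5 / 0.567 = 0.88 to 0.5 / 0.633 = 0.79 would appear as no difference.

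**Common routes only.** Recorded risk is p × s in each arm, so the ratio under equal true risk is 1.00.

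**The case against.** The strongest case on the other side has four parts.

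1. **The mechanism is not stated.** Sites report under the trials unit's procedures, which are not shown, and nothing says that therapists elicit or pass on adverse events. This stands, and is why the conclusion is that inflation may occur. There are plausible paths to the site, however. Sessions may take place in the MND clinic, therapists have fortnightly supervision, sessions are recorded with a tenth reviewed for fidelity, and confidentiality gives way to evidence of risk of harm.

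2. **Controls have other contacts.** Usual care is multidisciplinary and includes access to psychology and counselling, and only ACT participants are asked to refrain from other formal psychological therapy during treatment. The first part does not cancel the imbalance, because the ACT arm receives usual care too. The second could offset it to some degree.

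3. **The summary is descriptive, and the monitoring committee reviews all safety data.** Both are true. A by-arm table of a declared secondary outcome still invites comparison, and review by the committee does not equalise detection.

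4. **The source of a report is form-level detail that an article omits.** The full protocol, procedures and analysis plan are not shown and may already capture it. If so, only the tabulation needs wording. The point rests on the collection rule and the summary that the article does state.

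A reader might also infer that the comparison is bound to make ACT look harmful, or that the spurious ratio is 1.3 to 1.6. The latter comes from applying 30% to 60% therapist capture to all nine months (0.65 / 0.50 and 0.80 / 0.50). The article plans the sessions over four months, and a session cannot surface an event that has not yet happened.

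**Conclusion.** The point holds as a risk of unequal ascertainment. From this mechanism the bias runs one way, towards more recorded non-physical events in the ACT arm. Its size cannot be derived from the article. With 50% of events found by common routes, 30% to 60% of the rest found through therapy, even spread over nine months and therapy in the first four, the apparent ratio under equal true risk is about 1.13 to 1.27. It falls to 1.00 if therapy adds no reports or the common routes miss nothing, and rises somewhat if sessions overrun.

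The article does not support the stronger reading that ACT will look harmful. Therapist reporting is not stated, both arms share the follow-up assessments and usual care, and a real benefit could offset the excess. Nor does it follow that the safety table cannot be interpreted: it is descriptive, and can be read properly if the unequal surveillance is stated and a like-for-like table stands beside it.

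**What to change.** Record the source (6- or 9-month assessment, therapy session, other spontaneous report) and the date of each adverse event. Keep the planned by-arm summary of all events. Add a by-arm table limited to events elicited at the 6- and 9-month assessments, show therapy-session and other spontaneous reports separately, and state the unequal surveillance wherever the full table is interpreted. Reporting of serious adverse events is unchanged.

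The cost is one field, one table and a sentence or two in the analysis plan. The added table has fewer events, depends on recall over several months and omits people lost before 6 months (the sample size allows for 20% attrition by then). It also sets aside harms disclosed in therapy, and participants still know their allocation at those assessments. It should therefore supplement the full table and not replace it.

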### Ethics

The study has been approved by the London Dulwich Research Ethics Committee, Health Research Authority, and Health and Care Research Wales (19/LO/0272). Recruitment will only commence at a site when site-specific confirmation of capacity and capability has been obtained and the green light has been issued by the sponsor. Participants with MND, their caregivers and therapists will be consented in line with Sheffield CTRU SOPs and the Mental Capacity Act (2005). All participants will be asked to provide fully informed written consent, verbal consent (for those who cannot provide written consent), or consent via the use of a communication aid to participate in the trial. Participants will be made aware that their participation is voluntary and that they may withdraw from the intervention and/or trial, should they wish, at any time, without it affecting their rights. Participants may be withdrawn from the trial whenever continued participation is no longer in their best interests. Any amendments will be approved by the sponsor and communicated to all sites and the Health Research Authority. Compensation to those who suffer harm from trial participation will be available through UCL insurance.

### Dissemination

Dissemination to the academic and clinical community, plwMND and their families, and the broader public will occur through peer-reviewed, international, open-access academic journals, academic conferences, local clinical conferences and meetings, talks to local MND support groups and the MND Association, social media (e.g. University media releases, University website and Twitter feeds), and ACT training and seminars. In addition, the trial results will be reported in the ISRCTN database, and participants who have indicated they would like a copy of the results will be sent a summary of the findings. Standard author eligibility guidelines will be followed.

